### Study setting

The research will include individuals aged 65 years or older, of all genders, who meet the study’s inclusion criteria. Therapy sessions will be conducted individually and in person, in offices suited for psychological practice. Participants residing in senior housing will have the option, subject to agreement with their institution, to have sessions conducted in their facilities [22,23]. Each session will last one hour and occur weekly over a three-month period, resulting in a total of 12 sessions per participant, in accordance with the EFT protocol for resolving emotional injuries established by Meneses and Greenberg (2019), with adaptations presented below.

At the conclusion of the designated sessions, in accordance with the study plan and study procedures (Fig 1), assessment data will be gathered in paper format. When a participant misses a session, it will be rescheduled as soon as possible. The questionnaires will be completed after the sessions. If necessary, a member of the research team will assist participants in completing them in order to prevent fatigue. In all cases, the questionnaires (with their number based on previous study protocols involving older adults [32]) will be administered in distinct and varied sessions, with clear instructions, scheduled breaks, and diverse formats to minimize fatigue — regardless of significant variations in the participants’ individual schedules [29,32]. All collected data—including attendance records and dropouts—will be analyzed in accordance with the study protocol (intent-to-treat analysis versus treatment completers analysis), not only to inform the current analysis but also to support the design of future studies. It is expected that at least 70 participants will complete the intervention (more on this below), and any reasons for dropout will be systematically documented. Regarding the secondary objective, which focuses on the analysis of outcome variables, particular attention will be given to the data from participants who complete the full intervention (completers).

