### Participants

Our feasibility study will include a minimum total sample of 70 older participants, with 35 randomly allocated to the intervention group (IG) and 35 to the waitlist control group (CG) [22,29]. Although feasibility studies do not require large samples [33], they should adequately represent the target population and be sufficiently large to fulfill the study’s objectives. Authors [33,30,31] agree that feasibility RCTs typically recruit between 24–50 participants per arm on average, with the exact number depending on the specific aims and objectives of the study. Larger sample sizes may be necessary for more complex or ambitious goals (in accordance with the G*Power requirements for comparing two groups) [33,30,31].

Given the exploratory nature of our study—aimed at evaluating the feasibility and acceptability of the therapy, as well as obtaining preliminary insights into its potential effectiveness among the participants involved, rather than establishing causality or generating generalizable results—we determined that a sample size of 70 participants would be appropriate. This decision was informed by precedents in comparable feasibility studies [22,29,34], as well as by practical considerations such as recruitment capacity, budgetary constraints, and the minimum sample size required to adequately address feasibility-related objectives [35]. Based on all of this, we propose to include 80 individuals in our study to ensure that at least 35 participants complete each comparison group (minimum N = 70). Therefore, in line with other studies, an additional 15 percent of participants will be recruited to account for typical dropout rates [9,13].

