### Progression criteria

This study protocol will be developed for broader research based on the assessment of its acceptability and feasibility. Regarding the CEQ measure, the study will proceed without changes if the result is ≥ 6 on a 9-point Likert scale. The study will also progress without changes in the Session Satisfaction Module if the result is ≥ 3 on a 5-point Likert scale [22]. For recruitment, the progression criterion will be a rate of 75–100% of the sample size [61]. The criterion for retention level will be a rate >80% [36]. The progression criterion for the questionnaires will be a response rate >90%. For homework assessment, a score of ≥ 3 on a 5-point Likert scale will be required [22,29].

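### The 70-completer figure does not agree with the planned enrolment of 80 or with the progression criteria, and the recruitment criterion has no stated base

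*Protocol article*

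**What the plan says.** The Participants section gives 70 as a floor for the number randomised: "Our feasibility study will include a minimum total sample of 70 older participants, with 35 randomly allocated to the intervention group (IG"), with the other 35 on the waiting list. Later in the same section 70 becomes a number of completers. There the authors write "we propose to include 80 individuals in our study", and the stated purpose is "to ensure that at least 35 participants complete each comparison group (minimum N = 70"). The allowance behind the 80 is that "an additional 15 percent of participants will be recruited to account for typical dropout rates".

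Study setting repeats the completer reading: "It is expected that at least 70 participants will complete the intervention". The Abstract and Study design use 70 as the number to recruit.

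The reasons given for 70 are precedent, recruitment capacity, budget and "the minimum sample size required to adequately address feasibility-related objectives". No calculation is shown.

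Under Progression criteria, for recruitment "the progression criterion will be a rate of 75–100% of the sample size". For retention, "The criterion for retention level will be a rate >80"%. No base is named for the recruitment percentage, and no criterion refers to a number of completers. The Quantitative analysis section defines retention as therapy completers divided by those who started therapy.

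**The concern.** Recruitment and retention are primary feasibility indicators, and whether to progress is a main output of a feasibility trial. The figures that feed that decision should therefore have a single reading.

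They do not, in two respects. First, the promise of 70 completers is not what 80 enrolled would yield under the plan's own dropout allowance, and it yields still fewer at the retention criterion. Second, 70 stands both for recruits and for completers while 80 are to be enrolled, so a percentage of the sample size can be taken of either number. Two people applying the rule to the same recruitment count could report opposite results.

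**Working it through.** **Inputs.** Completer figure 70, i.e. 35 per group (Participants; Study setting). Number to enrol 80, i.e. 40 per group (Participants). Dropout allowance 15% (Participants). Recruitment criterion at least 75% and retention criterion strictly above 80% (Progression criteria).

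**1. Reproduce the 80.** Adding 15% to 70 gives 70 × 1.15 = 80.5, which matches the stated 80. Dividing by the expected completion proportion gives 70 / 0.85 = 82.4, i.e. 83, which does not match. The 80 therefore comes from adding 15% to the completers, not from allowing for a 15% loss among those enrolled.

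**2. What 80 enrolled delivers.**

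| Retention among 80 | Completers | Against 70 |
|---|---|---|
| 15% loss: 80 × 0.85 | 68 (34 per group) | 2 short |
| Smallest count above 80%: 65/80 = 81.25% | 65 | 5 short |
| Needed for 70: 70/80 | 70 | 87.5% retention |

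Reaching 70 allows a loss of at most 10/80 = 12.5%, which is less than the plan's own 15%. If retention only just exceeded 80%, 87 would have to be enrolled (0.80 × 87 = 69.6, so the smallest passing count is 70).

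**3. Recruitment pass mark by base.**
- Base 70: 0.75 × 70 = 52.5, so 53 recruits pass.
- Base 80: 0.75 × 80 = 60 recruits pass.
- With 53 recruits: 53/70 = 75.7% (pass) and 53/80 = 66.2% (fail).
- With 59 recruits: 59/70 = 84.3% (pass) and 59/80 = 73.8% (fail).

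Every count from 53 to 59 changes verdict with the base. On base 70 the planned 80 is 80/70 = 114%, outside the stated 75–100% band.

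**4. Smallest number of completers meeting both criteria, if every recruit starts therapy.** Take the recruitment pass mark R and the smallest integer above 0.80 × R.

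| Base | R | 0.80 × R | Completers | Retention | Wilson 95% interval | Below 70 by |
|---|---|---|---|---|---|---|
| 70 | 53 | 42.4 | 43 | 81.1% | 68.6–89.4% | 27 (39%) |
| 80 | 60 | 48.0 | 49 | 81.7% | 70.1–89.4% | 21 (30%) |

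For comparison, a bare retention pass with all 80 enrolled (65/80) has a Wilson 95% interval of 71.3–88.3%. The interval is about 17 points wide there, against 19 to 21 points in the table.

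**The case against.** A target and a progression threshold serve different purposes. Any threshold below 100% allows the target to be missed and the criterion met, so that alone is no contradiction. This stands.

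A reader might infer from the word minimum, and from the listed reasons for the sample size, that the protocol regards fewer than 70 as inadequate, so that the trial could progress on a sample its own plan rejects. The text does not support this. It calls 70 appropriate, names a required minimum as one consideration among several, and never equates that minimum with 70. It also cites 24–50 recruited per arm as typical, and 53–60 recruits (about 26–30 per arm) fall inside that range.

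It can also be argued that base 70 is the natural reading, because Participants and the Discussion attach the term sample size to 70. This has some weight but does not settle the matter. The criterion counts recruits, the number to be enrolled is 80, and 70 is used elsewhere for completers.

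The loss of precision is modest, as the interval widths show, and the protocol plans descriptive summaries without a precision target. The 43 and 49 are also extreme cases in which both criteria are only just met.

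Finally, one might require at least 70 completers before progression. That would be a preference about strictness, and it would clash with a pass mark of 60 recruits, since 60–69 recruits could never supply 70 completers.

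**Conclusion.** The point holds as a mismatch between stated figures. Enrolling 80 does not ensure 70 completers: it gives 68 at the plan's own 15% loss and 65 at a bare retention pass, against a required retention of 87.5%. The recruitment criterion has two readings, and these give opposite results for 53–59 recruits. Both criteria can be met with 43 completers on base 70 or 49 on base 80.

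The last two numbers assume that every recruit starts therapy. Because retention is counted among therapy starters, losses from the waiting list before therapy could make the passing number lower. The other progression criteria (credibility and expectancy, session satisfaction, questionnaire response, homework) must also be met, but they do not change these counts.

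This should be corrected before recruitment starts. It does not show that the sample is too small for the feasibility objectives.

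**What to change.** - **Progression criteria:** name one base for the recruitment percentage. Use the number to be enrolled, 80, because the criterion counts recruits; the pass mark is then 60.
- **Abstract and Study design:** make the number to be recruited agree with that base.
- **Participants:** replace the wording that 70 completers are ensured and are a minimum with a target or an expected number, which is 68 of 80 at 15% loss. Bring the matching sentence in Study setting into line.
- **Participants or Progression criteria:** state the smallest number of completers compatible with progression. On base 80 this is 49, with a Wilson 95% interval for retention of about 70–89%, assuming that every recruit starts therapy.

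The cost is a few sentences and no extra participants. The downside is a slightly less favourable stated completer figure.

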### Recruitment

Client recruitment (not started yet) is planned to start in 2026, upon securing external funding. The recruitment, selection, and randomization process will be managed by an independent psychologist. Recruitment strategies include distributing posters and flyers in locations such as supermarkets, pharmacies, and senior living facilities, as well as through social media. The purpose of the recruitment posters and flyers is to inform and invite potential participants to engage in EFT, specifically targeting individuals over 65 years of age who have experienced interpersonal offenses. The central question posed will be: “Have you been the target of an injustice in the past that may still be affecting you emotionally?”

Those who express interest will be invited to a preliminary interview, conducted either in person or via phone/videoconference [29,36]. After obtaining a written consent, eligible individuals will be evaluated in a comprehensive assessment to confirm that they meet the study’s inclusion criteria. This includes administering the Structured Clinical Interview for DSM-5–Research Version (SCID-5-RV) to assess mental health conditions and MoCA to screen various cognitive domains [29,37,38].

### Randomization

Participants will be randomly assigned to either the immediate IG or the waitlist CG using a computer-generated block randomization method to minimize bias and ensure equitable allocation between groups [22,36,39]. Randomization will be enhanced through stratification based on key participant characteristics—age, gender, educational level, and spirituality—to ensure a balanced distribution across both groups [9,29]. The CG will not receive any information about the therapy or recommendations to preserve the integrity of the CG. The allocation process will be double blinded, with group assignments concealed from both the principal investigator and the participants (Fig 2) [27,39].

**Fig 2 pone.0345792.g002:**
[figure not shown]
Overview of study processes.

### Therapy

Participants will be offered twelve in-person sessions, scheduled once a week. The therapy is structured into five phases (Table 2), following the protocol proposed by Meneses and Greenberg (2019). This approach emphasizes emotions in the therapeutic process and addresses the primary difficulties reported by adults in relation to forgiveness. Each session will be adapted to meet the specific needs of the clients.

**Table 2 pone.0345792.t002:** EFT for the resolution of emotional injuries session: An overview.

Phase	Content	Home Practice
Phase I:	Creating an alliance	Diary of feelings towards the injurer.
Phase II:	Evocation and exploration	Particular attention can be given to awareness of emotional experiences
Phase III:	Self-interruption work Empty-chair work	Drafting the letter to the injurer and its response (for personal use only); encouraging reflection and the identification of difficulties in forgiveness
Phase IV:	Empowerment and letting go or forgiving	Narratives of new meanings of the experience and the injurer
Phase V:	Termination	

#### Phase I: Creating an alliance.

The initial phase of therapy emphasizes the establishment and reinforcement of the therapeutic alliance to cultivate a safe, exploratory, and empathic environment. This phase is used to validate the emotional injury reported during the initial assessment and to clarify its most challenging aspects, through an empathic attunement to painful aspects of the interpersonal offense and painful emotions [2]. The therapeutic process dynamics are presented to the client, emphasizing the focus on difficulties arising from the experienced offense. Once the client feels ready, the therapeutic relationship is sufficiently solid, and the marker of an unresolved, emotional injury related to a past interpersonal situation is identified, the empty chair task can be introduced [19,40]. This task involves the client visualizing the injurer in an empty chair, to facilitate the exploration, awareness, expression, and processing of painful, core primary emotions to address unmet needs and resolve emotional injuries [20,40]. It is a collaborative process between the therapist and the client, with a particular emphasis on transforming the primary emotions associated with the emotional injury [2,7].

#### Phase II: Evocation and exploration.

The second phase of therapy primarily involves accessing and addressing problematic emotional processes and the needs that may arise from them. Therapists try to identify emerging markers, namely, feelings of pain, sadness, anger, vulnerability that clients may feel when remembering what happened or what offended them [2,20]. Along with the empathic and exploratory stance of the therapeutic process, the empty chair task continues to be proposed when markers of unfinished business appear, to help participants deal with the lingering feelings of pain due to the emotional injury. The task facilitates the arousal and exploration of emotions, recognition and differentiation of feelings, and the identification of various forms of anger. It can also assist clients in identifying secondary or non-adaptive emotions while accessing primary emotions [20]. Thus, the empty chair task can facilitate clients’ connection with and expression of their unmet emotional needs [2,8].

#### Phase III: Self-Interruption work.

The interruption of experienced emotions is a prevalent challenge in addressing unfinished business through the empty-chair task [2,40]. Consequently, there is often a necessity to address self-interruptions during the deepening phase of the empty chair task. So, this third phase specifically aims to assist participants in recognizing markers of self-interruption, typically manifested as emotional constriction, resignation, or hopelessness [2]. To deal with self-interruptions, we employ the therapeutic task of two-chair enactment, which entails engaging in an imaginative dialogue between different parts of the self: the part that interrupts or obstructs and the experiencing self, who endures the consequences of this interruption [40]. Through this approach, clients can gain awareness and access how they self-interrupt, and through which processes self-interruptions occur, often rooted in experiential avoidance of more painful emotions. This enables to address, among other emotional processes, feelings of hopelessness and discouragement that may emerge from the self-interruption process [2].

#### Phase IV: Empowerment and letting go or forgiving.

This stage of the process aims to deepen emotional processing through the empty-chair task, by accessing painful, chronic (primary maladaptive) emotions, and their underlying unmet needs [20,41]. This emotional deepening process can facilitate the recognition and expression of the core pain [2,41]. Therapists aim to facilitate clients’ mourning of unmet needs, promoting opportunities to fulfill those needs, and fostering new emotional experiences (such as compassion and pride in oneself) and new perspectives on the offense and the injurer [2]. The forgiveness process usually involves experiencing new emotions (e.g., empathy towards the injurer) and changing the view of the injurer, that becomes softened, for example, through an understanding of the reasons underlying the offense. The emotional transformation of resentment can happen through an emotional response that involves compassion and love [2]. The process of resolving emotional injuries can also be achieved through *letting go*, which is understood as a process involving the addressing of unresolved emotional needs and feelings related to the offense and the offender. *Letting go* entails acknowledging and working through the emotional impact—such as pain, resentment, or anger—without necessitating the development of empathy or positive feelings toward the offender. In contrast to forgiveness, which typically involves a relational shift toward the offender, *letting go* focuses on internal emotional healing, aiming to alleviate distress while maintaining personal psychological boundaries [2].

#### Phase V: Termination.

The therapy seeks to address several key dimensions: the client’s role as an agent of their own emotions; the experience of change as a continuous process; the acceptance of separation and loss; and the prevention of potential relapses [2]. Ultimately, the therapeutic process aims to culminate in forgiveness, which involves an adjusted regulation of the expression of resentment, anger, and shame associated with the offense, alongside the promotion of compassion. Alternatively, the therapy may conclude with a process of letting go, which entails a thoughtful processing of unmet needs and feelings related to the offense and the offender, without necessarily fostering empathy or compassion toward the latter [2].

### Anticipated adjustments of this protocol for older populations

Considering the current literature [6,14], including our own studies [18,19], we estimate that the older population may face specific difficulties in the process of forgiveness and resolution of emotional injuries. So, we anticipate a set of specificities and adaptations to the Meneses and Greenberg (2019) protocol.

#### Phase I specificities.

Studies indicate that psychosocial difficulties, such as social isolation or elder abuse [17], can lead individuals to minimize interpersonal offenses and their respective emotional injuries [6]. For example, a person who is dependent upon a family member may not express their true feelings and may (superficially) forgive to avoid negative interpersonal consequences. While recognizing the importance of valuing current relationships, therapists may need to facilitate clients’ awareness of the significance of acknowledging their own suffering and the negative consequences of emotional injury, as blocking the emotional process can lead to additional problems (much like the contrast between normative versus complicated grief, as proposed by Sharbanee & Greenberg, 2023).

To address this issue, we propose that therapists undertake experiential formulation and focusing as a therapeutic strategy aimed at highlighting the importance and value of accessing avoided emotions, alongside the promotion of greater self-awareness and self-acceptance throughout the therapeutic process and beyond [20,41]. This aims to explore client difficulties in experiential terms, emphasizing therapy’s focus on personal feelings and not necessarily on changes on relationships (i.e., forgiveness does not imply reconciliation) [22]. Indeed, the intention is to allow individuals to access their experiences more freely and authentically, without necessitating behavioral changes or causing negative repercussions [18,19,41].

#### Phase II specificities.

Previous studies by the present authors [18,19] have identified specific difficulties (or markers) that older individuals may face in the process of forgiving. One such difficulty is avoiding painful experiences by being purely conceptual. For instance, an older person might say, “I feel neither anger nor sadness [...] Forgiving is like lifting a weight off my shoulders [...] I don’t feel the need for support or affection.” This type of narrative is often characterized by an overly intellectualized self-voice that suppresses a more vulnerable, experiential voice, which may signal the presence of self-interruption [18,20,41]. In therapy, tasks such as empathic exploration [40] and focusing [42] can be proposed to encourage grounding in the experience. Subsequently, the two-chair enactment task [43,44] can be employed to facilitate dialogue between the dominant voice and the disowned voice.

